In each of the linear-mixed models, we entered the outcome measure of interest as the dependent variable. The time-points of the intervention, treatment arm, and an interaction term between time-points and treatment arm were treated as the independent variables. Covariates for all the models included the baseline values of the respective outcome variable, age, sex, and years of formal education. We also collected measures for other covariates relevant to MCI and dementia, including the geriatric depression scale (GDS) and geriatric anxiety inventory (GAI) clinical cut-offs, history of cardiovascular diseases, and history of myocardial infarction. These additional covariates were explored to examine their effects on the basic models, using the model fit statistics, namely the Akaike information criterion (AIC) and Bayesian information criterion (BIC) values. In the final models, for the additional covariates, only the significant ones for each model were retained. We based all the analyses on the intention-to-treat principle, hence all the participants who had measures at at least one time-point were included in the analysis. All statistical analyses were and will be further performed using the Statistical Package for the Social Sciences (SPSS) Statistics for Windows, version 23.0 (IBM Corp., Armonk, NY, USA). A two-tailed *p*-value of < 0.05 was and will be considered statistically significant.

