### 4.2. Implementation (Randomization Outcome): Balance in Baseline Variables

There were no significant differences in all baseline variables, including age, sex, and education levels (Table 2). All randomized participants attended the intervention groups that they were initially randomized to.

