**Figure 4 ijerph-18-10205-f004:**
[figure not shown]
CONSORT 2010 Flow diagram for co-primary outcome measures.

**Table 1 ijerph-18-10205-t001:** A summary of assessments or measures collected throughout the three time-points.

Assessments or Measures	Baseline	At 3-Month	At 9-Month
Social-demographic Questionnaire	√	-	-
Basic Health Screening	√	√	√
Physical Assessments (ADL and IADL)	√	√	√
Mini Mental State Examination (MMSE)	√	√	√
Depression and Anxiety Screening Tests (GDS and GAI)	√	√	√
Clinical Dementia Rating (CDR) Scale	√	√	√
Neurocognitive Tests	√	√	√
MRI Brain Scan	√	√	-
Blood Sample	13 mL	8 mL	13 mL
Urine Sample	15 mL	-	15 mL
Fecal Sample	√	√	√
Saliva Sample	√	√	√

ADL = Activities of Daily Living; IADL = Instrumental Activities of Daily Living; MMSE = Mini-Mental State Examination; GDS = Geriatric Depression Scale; GAI = Geriatric Anxiety Inventory; CDR = clinical dementia rating; MRI = Magnetic Resonance Imaging.

**Table 2 ijerph-18-10205-t002:** Comparisons of the baseline demographic and characteristics between participants in the Mindful Awareness Practice (MAP) and Health Education Program (HEP) Arms (N = 55).

Baseline Demographics and Characteristics	MAP, Treatment; n (%) or Mean (SE) (n = 28)	HEP, Control; n (%) or Mean (SE) (n = 27)	*p*-Value
Age (in years)	71.89 (1.14)	70.67 (1.19)	0.46
Sex			
Male	8 (28.60%)	6 (22.20%)	0.59
Female	20 (71.40%)	21 (77.80%)	
MCI subtypes			
aMCI	13 (46.40%)	8 (29.6%)	0.27
Non-aMCI	15 (53.6%)	19 (70.4%)	
Years of Formal Education	5.27 (5.02)	3.44 (4.27)	0.16
Ethnicity			
Chinese	27 (96.40%)	27 (100%)	1.00
Indian	1 (3.60%)	0 (0%)	
Others	0 (0%)	0 (0%)	
Employment Status			
Retired	14 (51.90%)	11 (40.70%)	0.14
Full-time worker	0 (0%)	0 (0%)	
Part-time worker	0 (0%)	4 (14.80%)	
Housewife	13 (48.10%)	12 (44.40%)	
Marital Status			
Single	1 (3.70%)	0 (0%)	0.29
Married	18 (66.70%)	14 (51.90%)	
Divorced	2 (7.40%)	1 (3.70%)	
Widowed	6 (22.20%)	12 (44.40%)	
MMSE (Total Scores)	24.59 (0.63)	24.70 (0.75)	0.91
GDS			
<5	18 (64.30%)	22 (81.50%)	0.15
≥5	10 (35.70%)	5 (18.50%)	
Attendance rate (%)	88.6 (12.48)	87.0 (19.11)	0.77
Total number of metabolic disorders	1.44 (0.22)	1.52 (0.16)	0.79
Presence of diabetes	6 (22.2%)	8 (29.6%)	0.76
BMI, kg/m^2^	24.76 (0.85)	24.06 (0.67)	0.53
Total number of chronic diseases	2.04 (0.33)	2.85 (0.25)	0.66
Total number of medications taken	2.89 (0.44)	2.96 (0.39)	0.90
Total number of participants taking psychotropic medications	1 (3.70%)	0 (0%)	1.00

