Abbreviations: aMCI = amnestic MCI; non-aMCI = non-amnestic MCI; BMI, body mass index; MMSE, Mini-Mental State Examination; GDS, Geriatric Depression Scale; clinical cut-off for GDS is 5, with those ≥5 suggesting probable depression.

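### GDS and GAI are offered to the mixed models only as clinical cut-offs although both scales are administered at baseline, so some adjusting information is lost at a small cost to the arm comparison

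*Protocol article*

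**What the plan says.** Section 3.10 of the protocol article has two tiers of covariates. The fixed tier is: "Covariates for all the models included the baseline values of the respective outcome variable, age, sex, and years of formal education". The second tier is optional and names depression and anxiety in dichotomised form: "including the geriatric depression scale (GDS) and geriatric anxiety inventory (GAI) clinical cut-offs". These additional covariates are explored with AIC and BIC, and "only the significant ones for each model were retained".

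Table 1 has a row for "Depression and Anxiety Screening Tests (GDS and GAI") with a tick at baseline, 3 months and 9 months. The Table 2 footnote defines the GDS split: "clinical cut-off for GDS is 5, with those ≥5 suggesting probable depression". Table 2 reports GDS only as below 5 or at least 5, and gives no GAI figure. Section 4.2 summarises the baseline comparison: "There were no significant differences in all baseline variables, including age, sex, and education levels".

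**The concern.** A covariate earns its place by explaining outcome variance and by removing chance imbalance between the arms. An indicator at a clinical threshold does both less well than the score behind it. It treats a GDS of 0 like a 4, and a 5 like the scale maximum. The article gives no reason for this form, while age and years of education are named in the same paragraph without any cut-off.

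The form matters most when the factor is imbalanced and the trial is small. Here the shares at or above the GDS cut-off differ by 17.2 percentage points. Section 4.3 reports 10 + 8 = 18 participants lost for psychometric measures at 9 months, which leaves 55 − 18 = 37. At stake are a little precision and a little residual imbalance in the estimated arm effect.

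**Working it through.** **Inputs.** From Table 2: GDS at or above 5 in 10/28 (MAP) and 5/27 (HEP), together 15/55. From Section 3.10: planning effect 0.5 (metric not named, taken here as SD units), 24 per arm, 5% level, and baseline outcome in every model. Assumed, because the article does not give them: the shape of the GDS distribution, its slope on outcome, and the pre-post correlation of the outcome.

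**1. The plan's own figure.** For 10/28 against 5/27, a Pearson chi-square without continuity correction gives 2.05, p = 0.152, which matches the printed 0.15. The difference is 35.7% − 18.5% = 17.2 points (95% CI −5.8 to 40.2), a standardised difference of 0.39.

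**2. Information kept by the GDS cut-off.** For a normal score linearly related to outcome, the share of explained variance kept is φ(z)² / [p(1 − p)].
- p = 15/55 = 0.273, z = 0.605, φ(z) = 0.332.
- 0.332² / (0.273 × 0.727) ≈ 0.557, so about 56% is kept and 44% lost.
- With right-skewed integer scores (beta-binomial on an assumed 0 to 15 range), 64% to 72% is kept when matched to the pooled share, and 69% to 78% in a second set matched to each arm's share.
- Across all of these the loss runs from about 22% to 44%.

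For GAI nothing can be computed, because no distribution or share above a cut-off is reported. For a normal score the loss would be 36% with half the participants above the cut-off, 51% with 20% and 66% with 10%.

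**3. Imbalance left in the score.** Under normality the two shares correspond to a latent arm difference of 0.896 − 0.366 = 0.53 SD, with an approximate 95% interval of −0.20 to 1.26. Regressing the latent score on arm and cut-off, by simulation, leaves 0.24 SD. Under the skewed scores matched to each arm, about 0.12 to 0.18 SD is left.

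**4. Imbalance left in an arm contrast on the outcome.** Take the normal case and an assumed outcome slope of 0.2 to 0.4 SD per SD of GDS.
- Cut-off as the only adjuster: 0.2 × 0.24 ≈ 0.05 to 0.4 × 0.24 ≈ 0.10 SD.
- Adding the baseline outcome, as Section 3.10 does in all models (simulated):

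| Assumed pre-post correlation | SD left in the arm contrast |
|---|---|
| 0.5 | 0.03 to 0.05 |
| 0.7 | 0.01 to 0.03 |
| 0.8 | 0.01 to 0.02 |

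Relative to the planning effect this is 0.01/0.5 = 2% to 0.05/0.5 = 10%.

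**5. If the test is the arm-by-time interaction.** With baseline among the modelled time-points, a baseline covariate entered as a main effect cancels from the interaction. In a random-intercept simulation with complete data, the interaction was identical with no GDS term, the cut-off or the score. With about one third missing at the last visit, the estimates differed by about 0.001.

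**6. Precision.** For a simple two-group comparison with d = 0.5 and 24 per arm, the residual variance is 1 − r² with the score and 1 − 0.557r² with the cut-off.

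| Score-outcome correlation r | Residual variance higher with cut-off by | Power, score | Power, cut-off |
|---|---|---|---|
| 0.2 | 1.8% | 42.4% | 41.7% |
| 0.3 | 4.4% | 44.3% | 42.7% |
| 0.5 | 14.8% | 51.6% | 46.3% |

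Only the gap between the last two columns bears on this point. The level of power is a separate matter.

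**The case against.** The case for leaving the plan alone has real substance.

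- **The baseline outcome is already in every model.** This stands, and it is why the residual is 0.01 to 0.05 SD. A reader who multiplied the slope by the remaining latent difference would infer 0.05 to 0.10 SD, or 10% to 20% of the planning effect. That leaves out a covariate the article fixes.
- **The arms do not demonstrably differ.** This also stands. A reader might infer from 35.7% against 18.5% that the arms differ in depression. The split is compatible with chance, and the latent 0.53 SD is a back-calculation with an interval that includes zero. Nor can one say the arms differ most at this cut-point, because it is the only one reported. Significance is still not the test of whether a covariate is worth adjusting for: a standardised difference of 0.39 makes GDS a sensible adjuster if it is prognostic.
- **The loss depends on the score's shape.** A reader might infer that close to half of the adjusting value of both scales is thrown away. The 44% needs normality and linearity and concerns GDS only. It refers to the covariate's own explained variance, not to trial power.
- **The covariates are optional.** Where GDS or GAI is not retained, its form does not affect the final model. Where it is itself the outcome, its baseline value is already a covariate. However, a weaker, dichotomised covariate is also less likely to pass the retention rule, so the form can influence whether GDS is adjusted for at all.
- **The cut-off has clinical meaning.** True, and it is a defensible way to describe the sample. That does not make it the better adjuster.

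**Conclusion.** The point holds as a minor efficiency improvement. Section 3.10 fixes a dichotomised form for two scales that are administered at baseline, and information is lost whenever that form is used. For GDS the loss is about 22% to 44% of the covariate's explained variance; for GAI the principle applies but no size can be given.

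The consequence for the arm comparison is small: about 0.01 to 0.05 SD of residual imbalance, assuming slopes of 0.2 to 0.4, pre-post correlations of 0.5 to 0.8 and a normal score. It is practically nil for an arm-by-time interaction when baseline is a modelled time-point; the article does not say which coefficient carries the test. The power cost is about 1 to 2 points at correlations of 0.2 to 0.3, and about 5 points only if the correlation is near 0.5. Nothing here shows that the trial's conclusions are biased or that randomisation failed.

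**What to change.** In Section 3.10, state that where GDS or GAI is used as a covariate, the baseline score enters as a continuous term. Keep the cut-offs for describing the sample in Table 2 and, if wanted, for a sensitivity analysis.

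No new data collection is needed, since both scales are administered at baseline. The change is not free, however. The Trial Status section says that part of the analyses is complete and published, so models that used the cut-offs would need refitting. The change should also be labelled as made after the baseline data were seen, with results under both forms reported where an earlier analysis used the cut-off.

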## Abstract

Background: With an aging population, developing non-pharmacological interventions (NPIs) to delay dementia has become critical. Apart from cognitive decline, dementia is associated with multiple pathophysiology, including increased oxidative stress, dysregulated gene expressions, cytokine, neurotrophin, and stress markers, telomere shortening, and deteriorations in brain connectivity. Although mindfulness practices have been proposed to ameliorate these biological changes, no empirical studies were conducted. We thus aimed to investigate the effects of mindfulness awareness practice (MAP) to prevent cognitive decline and improve peripheral biomarkers in community-dwelling older adults diagnosed with mild cognitive impairment (MCI). Methods/Design: This was a single-blinded and parallel-group randomized controlled trial with two arms (intervention and active control arms), conducted over nine months. A total of 60 consenting community-dwelling older adults diagnosed with MCI were planned to be randomized in a 1:1 ratio to either the MAP or the Health Education Program (HEP). Interventions were performed weekly for the initial 12 weeks, and monthly for the subsequent six months. Outcome measures were assessed at baseline, 3-month, and 9-month post-intervention by blinded assessors. Primary outcomes were neurocognitive tests, comprehensive peripheral biomarkers, and brain imaging scans. Secondary outcomes included basic health screening measures, affective symptoms, and measures of physical functions. Linear-mixed models were used to examine the effects of MAP on these outcome measures. Significance: This is the first randomized controlled trial to systematically investigate the effects of a mindfulness intervention in improving cognitive functions and various biomarkers in community-dwelling older adults diagnosed with MCI. Our findings have the potential to inform mindfulness intervention as a novel approach to delay dementia.

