## 2. Aims

To address these gaps in knowledge, we conceptualized this parallel-group randomized control trial (RCT) to investigate the effects of a mindfulness intervention. We named it the Mindfulness Awareness Program (MAP), with community-dwelling Asian older adults clinically diagnosed with mild cognitive impairment, examining comprehensive outcome measures. We aimed to determine the effects of MAP compared to a Health Education Program (HEP), the active control arm, on (1) delaying or reversing cognitive decline amongst older adults diagnosed with MCI, (2) neuroimaging and comprehensive peripheral biomarkers associated with MCI, and (3) affective symptoms, namely depressive and anxiety symptoms, and physical functioning measures.

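### The final models keep extra covariates by significance, outcome by outcome, and the GDS and GAI cut-offs among them are not limited to baseline values

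*Protocol article*

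**What the plan says.** Section 3.10 (Statistical Analysis) builds each linear-mixed model in two stages.

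- **Basic model.** It contains time-point, arm and their interaction, with a common adjustment set: "Covariates for all the models included the baseline values of the respective outcome variable, age, sex, and years of formal education".
- **Additional covariates.** Further measures were collected, "including the geriatric depression scale (GDS) and geriatric anxiety inventory (GAI) clinical cut-offs, history of cardiovascular diseases, and history of myocardial infarction". On their use: "These additional covariates were explored to examine their effects on the basic models, using the model fit statistics", namely AIC and BIC. Then: "In the final models, for the additional covariates, only the significant ones for each model were retained".

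The selected models are the ones called final. No unselected model is named as the main analysis.

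Depressive and anxiety symptoms are also a target of the intervention. They form Aim 3 in Section 2, and the Abstract states: "Secondary outcomes included basic health screening measures, affective symptoms, and measures of physical functions". Table 1 ticks GDS and GAI at baseline, 3 months and 9 months.

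**The concern.** Three features of the stated rule cause the difficulty.

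1. Whether a covariate enters depends on its p-value in the same data that give the arm effect. The final standard errors and p-values treat the chosen set as if it had been fixed.
2. The choice is made separately for each model, so two outcomes in one trial can be adjusted for different things. AIC/BIC and significance are also different criteria, and no rule covers disagreement between them.
3. GDS and GAI status are candidate covariates and also outcomes. Section 3.10 says baseline for the outcome's own covariate but sets no such limit on the GDS and GAI cut-offs, and makes no exception for the GDS and GAI models. A baseline cut-off would largely repeat the baseline score already in those models. A post-baseline cut-off would adjust an outcome for itself there, and elsewhere would remove effects that run through mood.

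At stake is whether a reader can take each arm estimate as the result of one defined analysis, in a trial with many outcomes and 37 to 40 participants followed to 9 months for the psychometric and fluid measures.

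**Working it through.** **Inputs from the article.** Randomized: 28 MAP, 27 HEP (Table 2). Psychometric losses at 9 months: 10 and 8 (Section 4.3), leaving 18 + 19 = 37. Fluid biomarker losses: 9 and 6, leaving 19 + 21 = 40. Baseline GDS of 5 or more: 10/28 and 5/27, p = 0.15 (Table 2). Assumed effect size: 0.5 (Section 3.10).

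**1. Number of possible final models.** Four named candidates, each in or out, give 2^4 = 16 per outcome. The list is introduced as examples, so 16 is a minimum.

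**2. Reproducing the baseline GDS comparison.** Chi-square = 55 × (18×5 − 10×22)² / (28×27×40×15) = 929,500 / 453,600 = 2.05, p = 0.152. This matches the stated 0.15. The difference is 35.7% − 18.5% = 17.2 points.

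**3. What keeping or dropping GDS does to a simple arm difference.** The shift equals the GDS coefficient times the imbalance. For GDS to be kept, its coefficient must reach significance.
- All 55: the within-arm sum of squares is 10×18/28 + 5×22/27 = 10.50, so the SE is 1/√10.50 = 0.309 residual SD. With 48 degrees of freedom the threshold is 2.01 × 0.309 = 0.62. The shift is at least 0.62 × 0.172 = 0.11 residual SD.
- 37 participants, same imbalance assumed: the sum of squares is 10.50 × 37/55 = 7.07 and the SE is 0.376. The threshold is 2.04 × 0.376 = 0.77, and the shift at least 0.77 × 0.172 = 0.13 residual SD.
- The arm effect's own SE is √(1/28 + 1/27) = 0.270 and √(1/18 + 1/19) = 0.329, so the shift is about 0.4 of a standard error in both cases.

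This ignores correlation with the other covariates. It applies to an arm difference at follow-up, not to a change from baseline.

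**4. Type I error, single-visit ANCOVA.** Two simulations of 4,000 runs per scenario, 37 analysed, four binary candidates with assumed prevalences of about 0.10 to 0.27. Monte Carlo SE is √(0.05×0.95/4000) = 0.35 points.

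| Simulation | Fixed set | Significant ones kept |
|---|---|---|
| First | 5.1% (all four in) | 6.1% |
| Second, candidates unrelated to outcome | 5.8% (basic), 5.8% (all four) | 6.6% |
| Second, each candidate with effect −0.4 | 5.1% (basic), 5.4% (all four) | 6.5% |

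The increase is about one point. In the second simulation at least one candidate was kept in 18% of runs when none mattered and in 63% when each had effect −0.4.

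**5. Type I error, three-visit mixed model.** A participant-level covariate entered as a main effect largely cancels from a within-person change, so the time-by-arm contrast should hardly move. Two simulations of the 9-month contrast agree.
- 28 v 27 with the article's psychometric losses, correlation 0.6 assumed known, about 1,470 runs (SE about 0.6 points). Rejection was 5.5% with selection against 5.3% in the basic model for null candidates, and 4.8% against 4.0% for effect −0.4. Mean shifts were 0.003 and 0.012 SD.
- A second simulation gave 4.7% against 4.7% and 4.0% against 3.5%, with mean shifts of 0.002 to 0.009 SD. When baseline is a covariate and only follow-up visits are modelled, the 95th percentile of the shift rises to 0.08–0.10 SD.

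Section 3.10 speaks of three time-points and also adjusts for the baseline value, so either form could have been fitted.

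**6. Conditional case: post-baseline GDS and GAI.** With an assumed total effect of 0.50, half of it through mood, the mean estimate was 0.50 in the basic model, 0.41 after selection and 0.375 with all four covariates. With the whole effect through mood it was 0.50, 0.33 and 0.28. In a separate scenario with baseline covariates only, the estimate was 0.51 in every model.

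**The case against.** The strongest reply is that the rule does little harm. It looks at the covariate's significance and not the arm's, and the mixed model's time-by-arm contrast is almost untouched. That stands, and it limits the point to moderate weight. It does not answer the different adjustment sets across outcomes, or the shift of about 0.1 SD that can occur in a single estimate.

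A second reply is that GDS and GAI were probably taken at baseline. They are listed beside medical histories, Table 2 reports GDS in the same cut-off form as a baseline characteristic, and an article may leave the covariate's visit to a fuller document. This is fair. A reader might infer that mediator bias occurred; the article does not show it. What remains is that the current wording permits it. The selection rule itself is stated, so an unseen analysis plan does not excuse it.

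Two further inferences go too far. Choosing, from all subsets, the one most favourable to the arm effect gave 9% to 11% rejection in the single-visit simulations, but the article describes no such search and that is not this plan's error rate. Nor can the AIC and BIC comparisons be called invalid on grounds of restricted likelihood: the estimation method is not stated, and retention rested on significance.

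**Conclusion.** The point holds in limited form. The final models are selected from the outcome data, one outcome at a time, with p-values that take no account of it. The expected inflation of type I error is about one percentage point for a single-visit arm comparison and near zero for the time-by-arm contrast. An individual estimate can move by about 0.1 SD, roughly a fifth of the assumed effect of 0.5. Where GDS is the covariate kept, the baseline imbalance makes such a shift likely for a follow-up arm difference. These sizes rest on assumed prevalences, covariate effects and correlations, since the article gives only baseline GDS. The mediator problem is conditional on post-baseline values having been used. None of this invalidates the trial; it leaves the main analysis of each outcome undefined when it could easily be defined.

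**What to change.** - Make the basic model of Section 3.10 (baseline outcome value, age, sex, education) the main analysis for every outcome analysed by the mixed model, and delete the significance-retention step from it.
- Add one sensitivity model with all the named additional covariates entered together. State that GDS and GAI are baseline values, and omit GDS or GAI from its own outcome model.
- For outcomes already analysed or published, report the basic-model result beside the selected one.

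It is tempting to add MCI subtype and baseline GDS status to the main set because Table 2 shows imbalance in both. That would be another choice made after the data are in, and it is not needed.

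The cost is some re-analysis, including published outcomes, and slightly lower precision where a dropped covariate was prognostic. No new data are required.
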